#### Emergency unblinding

Emergency unblinding is not applicable in this trial. The medical officer assessing the patient’s foot/feet at 3 weeks and 3 months post-tenotomy is the only provider blinded to group allocation in this trial. If he/she believes the child requires additional assessment, because of inadequate progression during treatment, he/she can refer the child to the treating orthopedic surgeon for further assessment. The treating orthopedic surgeon is aware of the group allocation and will do all necessary assessments and will put the child’s health before the trial. This may include unenrolling the child from the trial, if necessary. The medical officer on duty will remain blinded to the group allocation for this respective child.

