#### Outcomes

Group A will be compared to group B for the primary and secondary analyses. A multi-level mixed-effects regression model will be used to assess the outcomes. An overview of the different variables to be assessed can be found in Table 1. A linear regression model will be used for the continuous variables and a logistic regression model for the binary variables. If a child received a tenotomy on both feet, these two feet will be clustered, and the analysis must make an adjustment for the lack of independence between measures on these two feet. A mixed-effects model allows for the inclusion of a random subject effect to the regression model, accounting for correlation between pairs of feet on the same child and also assessing the treatment effect from both between-subject differences and within-subject differences. Stata Version 17 (StataCorp, TX, USA) will be used for the analysis. A *p*-value < 0.05 will be considered significant. We will use the one-tailed *p*-value for all our analyses.

**Table 1 Tab1:** Clinical outcomes and proposed statistical analysis

Variable/outcome	Hypothesis	Outcome measure	Method of analysis

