**Primary outcomes**			
Dorsiflexion at 3 weeks post-tenotomy	Equal range of dorsiflexion	Degrees of dorsiflexion with 5° increments	Multi-level mixed effects linear regression
Dorsiflexion at 3 months post-tenotomy	Equal range of dorsiflexion	Degrees of dorsiflexion with 5° increments	Multi-level mixed effects linear regression

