#### Analysis population and missing data

We will test for non-inferiority using the “intention-to-treat” approach. All participants will be assessed as part of the group they were randomized to. Children who were randomized to group A: needle tenotomy and received a blade tenotomy instead because of a decision made at the treating physician’s discretion are excluded from the trial. Cross-overs from the blade to the needle tenotomy group are not a possibility in our trial, given that the blade tenotomy is the gold standard and the “experimental” needle tenotomy is not performed based on parents’ request or physician’s preference. Therefore, there is no valid reason to assess the data in a “per-protocol” fashion.

As stated earlier, given the follow-up duration of 1 year, we expect a drop-out rate of about 10%, and the sample size will be adjusted for this expected loss-to-follow-up. Previous research shows that drop-out is predominantly related to a mix of socio-economic and contextual factors and much less related to the level of correction of the deformity or the satisfaction of the parents [18, 23]. Missing data is therefore considered to be missing at random (MAR) and no dummy variable creation or imputation will be done as the mixed effects regression models provide valid estimates under MAR.

Children who missed out on both follow-up consultations and for whom we were not able to schedule a follow-up consultation within 6 months of the tenotomy will be excluded from the trial.

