Only de-identified data, using the trial tracking number for each foot instead of a personal identifier like the medical record number, will be shared with the research team. Age at time of tenotomy and at time of the two follow-up visits will be calculated by the program coordinator as to avoid sharing identifiable data such as a date of birth or a date of visit.

If a participant missed one of the required follow-up visits his/her parent/caregiver will be contacted to remind them of the importance of follow-up during clubfoot treatment. They will receive the standard phone call any patient in the clubfoot clinics receives when they miss an appointment. If a patient has not returned for follow-up after within 6 months of his/her last scheduled follow-up appointment, the patient’s enrolled foot/feet will be labeled as “lost to follow-up” for both the program’s purpose as well as for the trial’s purposes.

Participants’ data, including de-identified data, will not be shared with anyone outside of this trial without formal written consent of the parents/caregiver or the participant him/herself once they reach the age of 18 years.

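### The missing-at-random argument for no imputation does not fit the 3-month model as described: the 3-week value is not used, so loss must be unrelated to the 3-month outcome within each arm

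*Protocol article*

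**What the plan says.** Under Analysis population and missing data, the Protocol article assumes MAR, rules out dummy variables, and says that no "imputation will be done as the mixed effects regression models provide valid estimates under MAR". It supports this by citing earlier research in which drop-out was mainly socio-economic and "much less related to the level of correction of the deformity or the satisfaction of the parents".

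Table 1 lists "Dorsiflexion at 3 weeks post-tenotomy" and "Dorsiflexion at 3 months post-tenotomy" as two rows, each with its own mixed-effects linear regression. Under Data analysis and statistical methods, Outcomes, the text says: "A mixed-effects model allows for the inclusion of a random subject effect to the regression model". The purpose given is the correlation between the two feet of one child. No visit term, arm-by-visit term or correlation across visits is mentioned.

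The Trial design section and the Outcomes section that defines the endpoints make the 3-month value primary. Only children who missed both follow-up visits and could not be seen within 6 months are excluded, so a child seen only at 3 weeks stays in the trial.

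Emergency unblinding lets the blinded assessor refer a child who progresses poorly, at 3 weeks or 3 months, to a surgeon who knows the allocation. On what the surgeon may then do, it says: "This may include unenrolling the child from the trial, if necessary".

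**The concern.** A likelihood-based mixed model copes with MAR loss only when the observed data that predict the loss are in the model. If the 3-month model holds 3-month values alone, the only information left about an absent child would be the other foot. Visits are by child, so a missed visit normally removes both feet. The random effect then recovers nothing and the primary analysis is complete-case. It is valid if, within each arm, loss is unrelated to the 3-month outcome. The plan claims validity under a weaker condition than that.

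The direction matters in a non-inferiority trial. Suppose the needle truly gives less dorsiflexion and feet with a poor 3-week result are lost more often. More poor feet then go missing from the needle arm, the observed deficit shrinks, and a false declaration of non-inferiority becomes more likely.

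**Working it through.** **Inputs from the Protocol article.** SD 9.02°, margin 4°, alpha 5%, power 95% (Sample size and power calculation); one-tailed testing (Data analysis and statistical methods, Outcomes); blade mean 21.42° (Non-inferiority margin determination); expected drop-out about 10%.

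**Assumptions, because the document gives no figures.** True needle deficit 4° at both visits (needle mean 17.42°); correlation *r* between the 3-week and 3-month values 0.7; the same SD at both visits; normal values; feet treated as independent; loss before 3 months depends only on the 3-week value, by the same rule in both arms.

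**Step 1: the plan's own figure.** n per arm = 2 × 9.02² × (1.645 + 1.645)² / 4² = 110.1, rounded up to 111, so 222 feet. Adding 10% gives 222 × 1.10 = 244.2, which agrees with 244. The standard error of the difference with 111 per arm is 9.02 × √(2/111) = 1.211°.

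**Step 2: bias of the 3-month-only model.** Let feet below a cut-off c at 3 weeks be lost with probability L and the others with probability H. With z = (c − arm mean)/9.02, φ and Φ the normal density and distribution function, and R the proportion retained:

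- R = 1 − [L·Φ(z) + H·(1 − Φ(z))]
- upward shift of the retained 3-week mean = 9.02 × φ(z) × (L − H) / R
- shift of the retained 3-month mean = *r* × that shift

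Example with c = 10°, L = 30%, H = 5%:

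- Blade: z = (10 − 21.42)/9.02 = −1.266, Φ = 0.1027, φ = 0.1790. R = 1 − (0.30 × 0.1027 + 0.05 × 0.8973) = 0.9243. 3-week shift = 9.02 × 0.1790 × 0.25 / 0.9243 = 0.437°. 3-month shift = 0.7 × 0.437 = 0.306°.
- Needle: z = (10 − 17.42)/9.02 = −0.823, Φ = 0.2054, φ = 0.2844. R = 0.8987. 3-week shift = 0.714°. 3-month shift = 0.500°.
- Estimated deficit = 4 + 0.306 − 0.500 = 3.81°.
- False non-inferiority = Φ((4 − 3.806)/1.211 − 1.645) = Φ(−1.485) = 6.9%.

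**Step 3: other rules, *r* = 0.7, same rule in both arms.**

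| Loss rule at 3 weeks | Loss blade / needle / total | Estimate | False non-inferiority |
|---|---|---|---|
| <10°: 20%, otherwise 8% | 9.2% / 10.5% / 9.8% | 3.91° | 5.8% |
| <10°: 20%, otherwise 5% | 6.5% / 8.1% / 7.3% | 3.89° | 6.0% |
| <10°: 30%, otherwise 5% | 7.6% / 10.1% / 8.9% | 3.81° | 6.9% |
| <15°: 30%, otherwise 2% | 8.7% / 13.0% / 10.9% | 3.82° | 6.8% |

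In the third row, a correlation of 0.3 gives 3.92° and about 6%, and 0.9 gives 3.75° and 7.5%.

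**Step 4: a joint model of both visits.** When loss depends only on arm and the 3-week value, the regression of the 3-month on the 3-week value is the same in retained and lost feet. Averaging it over every 3-week value in the arm returns the full-arm mean, so the contrast is 4.0°. A simulation of the last rule (122 feet per arm, 8,000 runs, *r* = 0.7) gave false non-inferiority of 5.0% for the joint model and 7.0% for the 3-month-only model.

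**Step 5: when the problem vanishes.** With 10% loss unrelated to outcome, both models are unbiased. With no true difference and one rule in both arms, the two shifts cancel and the contrast is again unbiased.

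**The case against.** The article never says in words that the visits are fitted separately. Table 1 lists outcomes with a model class, not equations; dorsiflexion is recorded at both visits; children seen once are retained; and visit terms may stand in an analysis plan that is not shown. This has weight: if a joint model is intended, one sentence settles the matter. Still, the only purpose given for the random effect is the pairing of feet, so separate models are the likelier reading, and the MAR justification is printed in the article itself.

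The drop-out argument also counts. If loss is essentially socio-economic, as the plan mostly argues, the 3-month-only model is unbiased. But the plan says less related, not unrelated, and describes a route from poor progress to removal.

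Three stronger readings are tempting and are not supported.

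- **A larger error.** Losing half of the feet below 10° (otherwise 5%) gives about 9% false non-inferiority, and losing 90% gives about 17–18%. Those rules imply total loss of 11.9% and 18.1%, above the roughly 10% that the plan expects over a whole year, while the endpoint is at 3 months. If 3-week-driven loss acts in the needle arm only (36% below 15°, otherwise 2%; blade 10%), the error is about 20% at *r* = 0.7, but nothing in the document says that loss will differ in this way.
- **That poor feet will be lost more often.** The document permits this and gives no frequency. Removal is discretionary.
- **That a joint model cures such removal.** The surgeon knows the arm and makes further assessments. If the decision rests on more than the 3-week value, the joint model is not guaranteed to be valid either.

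A reader might also fault the lack of adjustment for pre-tenotomy dorsiflexion. That is unrelated to the MAR claim, its correlation with the outcome is not given, and eligibility (below 15°) restricts its range.

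**Conclusion.** The concern holds in this limited form. As described, the primary 3-month analysis is complete-case, and the stated reason for not imputing does not cover it. On the illustrative assumptions above, with total loss near the plan's own figure, a true 4° deficit is understated by about 0.1° to 0.2° and the one-sided 5% error becomes about 6–7%. That is modest, but it runs towards declaring non-inferiority. The result rests on an assumed visit correlation and assumed loss rules, on feet treated as independent, and on reading Table 1 as separate models. It is a correctable weakness of specification and no evidence that the trial's result will be biased.

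**What to change.** Make the primary analysis one linear mixed model of dorsiflexion at both visits. Use arm, visit and arm-by-visit as fixed effects, with foot nested within child and correlation across visits. Take the 3-month arm contrast and its confidence interval as the primary estimate for the comparison with 4°. State that children seen only at 3 weeks are retained in this model. Keep the 3-month-only model as a sensitivity analysis. If a joint model was already intended, say so beside Table 1.

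Reword the MAR sentence so that it refers to loss that depends on arm and the 3-week value, and do not claim that the model handles unenrolment decided on further findings.

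The cost is analysis wording and a slightly more complex model. Dorsiflexion is already recorded at both visits, so no new data are needed.

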### Outcomes

Patients will be followed as per the standard follow-up schedule at the Pehla Qadam clubfoot clinic. Patients will be evaluated at 3 weeks and at 3 months post-tenotomy during regular follow-up consultations. The dorsiflexion range at 3 months post-tenotomy is considered the primary outcome. These measurement points were chosen as they coincide with the standard follow-up appointments established at the Pehla Qadam clubfoot clinic. Given that long-term follow-up is challenging in low-resource settings, the primary outcome measure was the first follow-up visit after cast removal, i.e., 3 months post-tenotomy to minimize drop-out from the trial.

The primary outcome measure is as follows: range of dorsiflexion will be registered at both follow-up visits.

The secondary outcome measures are as follows: complications including neurovascular damage in the heel region, skin, and wound problems or infections will be recorded at both follow-up visits. Neurovascular damage, an infection requiring antibiotic treatment or any other type of complication that requires the consultation of another medical specialty, will be considered a major complication. Scar hypertrophy, local edema, or erythema will be considered minor complications.

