## Trial status

Enrollment in this trial began on 21 May 2021 and is estimated to be finished by September 2023. Follow-up of patients and data collection is planned to be finished by the end of December 2023. This protocol version is version 2, dated 31 March 2023. Enrollment of participants is ongoing at the time of submission.

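### Children who attend no visit are excluded from an analysis called intention-to-treat, which read literally drops their tenotomy-time complications, and the separate lost-to-follow-up label starts its clock elsewhere

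*Protocol article*

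**What the plan says.** The section on analysis population and missing data states that non-inferiority will be tested by intention-to-treat, with each participant assessed in the group assigned. Missing data are taken as missing at random and left without imputation. The section then sets an exclusion. It concerns "Children who missed out on both follow-up consultations" and for whom the team was "not able to schedule a follow-up consultation within 6 months of the tenotomy will be excluded from the trial".

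The section on data management, access and confidentiality has a second 6-month rule. It starts from a single missed visit: "If a participant missed one of the required follow-up visits his/her parent/caregiver will be contacted". It continues: "If a patient has not returned for follow-up after within 6 months of his/her last scheduled follow-up appointment", the "enrolled foot/feet will be labeled as" lost to follow-up, both for the clinic programme and for the trial. It does not say that the child is excluded.

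On outcomes, Table 2 lists minor and major complications at three times: at the tenotomy, at 3 weeks and at 3 months. The section on harms collects adverse events from enrolment onwards.

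**The concern.** Two things do not fit together.

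First, removing randomised and treated children because they did not attend is not intention-to-treat in the sense that the same section gives. For dorsiflexion the practical difference is slight. For complications it is not only a matter of words. A complication at the tenotomy is seen on the day, whether or not the family returns. If the child is then excluded from the trial, an observed safety event disappears from the comparison. In a non-inferiority trial of a new instrument, the count of such events in all feet operated on is part of the case for the technique.

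Second, the two 6-month rules start at different points and nothing reconciles them. The same child can be out of the trial under one section and still in follow-up under the other. The flow of participants and the reported number lost then depend on which section the analyst reads.

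**Working it through.** **Inputs.** Visits: "Patients will be evaluated at 3 weeks and at 3 months post-tenotomy during regular follow-up consultations" (Outcomes). Clocks: 6 months from tenotomy (analysis population) and 6 months from the last scheduled appointment (data management). Sample size 244 feet and drop-out about 10% (sample size section). Complication rate 2% from the literature (Introduction).

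**Step 1: where each clock ends, in months after tenotomy.**
- Exclusion rule: 6.
- Loss label, if the last scheduled appointment is the 3-week visit: 3 weeks is about 0.7 month, so 0.7 + 6 = about 6.7.
- Loss label, if it is the 3-month visit: 3 + 6 = 9.

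The end points differ by about 0.7 to 3 months, depending on which visit is meant.

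**Step 2: what happens to particular children.**

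| Child | Exclusion rule | Loss label |
|---|---|---|
| Missed both visits, nothing scheduled by month 6, returns at month 8 | Excluded | Not lost if counted from the 3-month visit; lost if counted from the 3-week visit |
| Missed both visits, nothing scheduled by month 6, returns at month 6.5 | Excluded | Not lost on either reading |
| Attended at 3 weeks, missed the 3-month visit, never returns | Stays in | Lost at month 9 |

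Exclusion and loss are therefore separate statuses that can disagree in both directions. Only the first column of rules removes anyone.

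**Step 3: effect on dorsiflexion.** A foot with no visit has no dorsiflexion value. A mixed model without imputation uses only observed values, so excluding the foot or keeping it with a missing outcome gives the same estimate.

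**Step 4: effect on tenotomy-time complications.** Expected drop-out is 0.10 × 244 = 24.4 feet. If every drop-out missed both visits, which is the extreme case, about 24 treated feet would leave the safety comparison. As an illustration, assume that the 2% literature rate applies to both arms and to the time of tenotomy. Then 0.02 × 244 = 4.9 events are expected in all, and 0.02 × 24.4 = 0.5 of them would fall in the excluded feet. The true number excluded should be smaller, since some drop-outs attend at 3 weeks.

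**Step 5: the calendar.** The trial status section puts the start of recruitment at 21 May 2021 and its expected end in September 2023. For closure it gives this plan: "Follow-up of patients and data collection is planned to be finished by the end of December 2023". A foot operated on 30 September 2023 reaches 3 months on 30 December 2023, just before closure. Its 6 months from tenotomy end on 30 March 2024. Assume even accrual over the 862 days from 21 May 2021 to 30 September 2023. The feet whose clock is cut short are then:
- exclusion rule (tenotomy after 30 June 2023): 92/862 × 244 = 26;
- loss label from the 3-week visit (after 9 June 2023): 113/862 × 244 = 32;
- loss label from the 3-month visit (after 31 March 2023): 183/862 × 244 = 52.

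These are all late feet. At 10% drop-out, about 2.6, 3.2 and 5.2 of them respectively would be drop-outs.

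**The case against.** The strongest reply is that the two rules do different jobs. One is an exclusion from the trial, triggered by two missed visits. The other is an administrative label, triggered by one. A child can hold both statuses without contradiction. This stands, as far as exclusion goes. A reader might infer that who is excluded depends on which section is used. The documents do not support that, because the data management section excludes nobody. What remains is that the label is expressly extended to the trial, so the two counts need a common start.

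A reader might also infer that late enrolees are held to a stricter rule because data collection closes in December 2023. The closing date is a plan in a status note, and it accommodates the 3-month visit of the last foot. The number of late drop-outs is about 3 to 5 under even accrual, and blocked 1:1 allocation should make it similar in both arms. No bias in the treatment difference follows.

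A third inference is that a value from month 8 will be analysed as the 3-month outcome. The protocol defines the endpoint at 3 months. Visit windows are commonly set in an analysis plan, which is not shown. The Discussion also gives the view that the tendon has healed and dorsiflexion has settled by 3 months. It leaves only walking as an influence of unknown size.

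Finally, adverse events are collected from enrolment, so tenotomy-time events would be recorded. That is true, but collecting an event does not keep it in the comparison once the child is excluded from the trial. This part of the concern is not answered.

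**Conclusion.** The point holds as a contradiction within the analysis section, together with an unreconciled start point in the data management section. The stated intention-to-treat analysis and the exclusion for non-attendance cannot both be followed literally. The consequence for the primary estimate is small, and nothing shows a difference between arms. The consequence for safety is that an observed key secondary outcome may be discarded for treated feet. The bound is about 24 feet if drop-out is 10% and every drop-out missed both visits. With events as rare as 2%, that is about half an expected event out of about five, an illustration that rests on applying the literature rate to both arms. The point is worth correcting because the remedy is nearly free, not because a large distortion has been shown.

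**What to change.** - In the analysis population section, replace the exclusion with a statement that the outcome is missing and the foot is kept in its allocated arm.
- State that tenotomy-time complications and adverse events are counted for every foot operated on, whether or not the child returns.
- Use one start point, time since tenotomy, for loss to follow-up in both the analysis section and the data management section.
- Report the actual time since tenotomy for any late measurement. The coordinator already computes age at tenotomy and at both visits, so this is a subtraction.

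The cost is wording and a small change to the participant flow table. No new data are required. Keeping data collection open past December 2023 would recover a few late returners at the price of a later analysis. It is optional and does not correct an error.
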